#### Cost-of-illness (COI) study as part of the Cohort study

A COI study will be performed to gain insight into care received after stroke and the economic consequences of psychosocial care in particular. A COI study aims at identifying and measuring all the costs of a particular disease, including the direct, indirect and intangible dimensions [35]. This COI study will be embedded in the Cohort study, focussing on the course of quality of life in stroke patients and their informal caregivers, and determining factors predicting quality of life, including pre-stroke health situation factors, stroke-related factors, personal factors and partner factors after stroke. As it is embedded in the Cohort study, the COI study will be related to outcomes of the cohort in a cost-outcome description.

### Sample size calculation

With an inclusion of 500 patients and an expected drop-out rate of 40%, 300 patients should be available for long term analysis (to identify early predictors of long term consequences). For instance, to analyse the course of reintegration and quality of life (linear regression analysis), a total of 300 patients allows regression models with 15 predictors and 15 to 20 subjects per predictor.

### Setting and participants

For the COI study 500 patients will be recruited from the stroke units in 6 participating hospitals in the Netherlands. If present, informal caregivers will also be recruited for the Cohort study to estimate levels of burden, though their presence is not a necessity for the COI study. Written informed consent for participation is obtained after recruitment.

### Timeline

Cost measurements are conducted at 2 months (T2), 6 months (T3), 1 year (T4) and 2 years (T5) post stroke, which is parallel to the measurement points of other questionnaires included in the Cohort study. Retrospective data covering a fixed period prior to measurement points will be extracted from the questionnaires: 2 months at T2, 4 months at T3, 6 months at T4 and 6 months at T5. To avoid recall bias after the two year follow-up, a fixed period of maximum 6 months prior to T5 is chosen. An overview of the timeline for the cost-of-illness cost measurements is presented in Figure 4.

**Figure 4 F4:**
[figure not shown]
**Cost measurement Cohort study**.

### Outcome measure

For the purpose of the COI study, necessary cost information will be retrieved through a specially designed short cost questionnaire of 11 items covering the costs of psychosocial care after stroke. A simple questionnaire is preferred, for the purpose of the COI study; accordingly the questionnaire has been adapted from previous trial-based economic evaluations studies.

The questionnaire consists of 3 subscales: health care costs, productivity costs and costs of informal care. The dimension of health care costs is captured with 8 items, productivity costs with 2 items and costs of informal care with 1 item. Care received will be measured in absolute numbers, representing visiting times and hours, day and nights spent on health care services and informal care. Due to the fact that the questionnaire is adjusted to be disease-specific every time it is being used, no research has been done on the validity of this questionnaire for stroke research. Nevertheless, the validity of self-reported measurements has been proven earlier in a large multi-centre clinical trial [36].

### Cost analysis

Essentially, there a two approaches to establish the costs of illness: the top-down approach and the bottom-up approach [37]. Scientific publications so far show that the majority of COI studies have been performed using a top-down method, based on calculating the costs of a disease through national databases [8]. The COI study described in this article is designed to use a bottom-up method in which a group of patients who have suffered from a stroke (the cohort population) will be asked what the costs of their disease are, through a specially designed cost questionnaire, instead of using databases. The estimation of costs will be divided into two steps. The first step is estimating the quantity of health inputs used and the second step is to estimate the unit costs of the inputs used [38]. The costs are then estimated by multiplying unit costs by the quantities. One of the main advantages of the bottom-up approach is that detailed data can be obtained regarding costs outside the health care sector such as the productivity losses, which will be investigated in this study [37]. Other advantages are that the bottom-up approach is much more accurate in measuring costs than the top-down approach, which is more likely to present misallocation of costs [38]. For example, national health care expenditures may either under or overestimate the total direct costs, where the bottom-up approach gives a more accurate estimate. Furthermore, a serious problem with the top-down approach is that all costs are attributed to the primary diagnosis [37]. This is a serious problem considering that a relevant part of all hospital discharges involve patients with multiple diagnoses. This is not an issue, and therefore an advantage, with the bottom-up approach. In addition, a follow-up period of 2 years will be used in this study, which will make it possible to distinguish patterns in health care consumption over time.

### Valuation

Within the COI study, the valuation of health care consumption, productivity losses and the costs of informal health care will be similar to the trial-based economic evaluation. This means that the valuation in general will be based upon the Dutch manual for cost analysis in health care research [39].

### Statistical analysis

Missing data and skewed data will be handled similar as in the economic evaluation study, hence respondents for whom at least 75% of the data per measurement instrument are available will be included in the analysis and missing data on item level will be handled using SPSS missing value analysis. Completely missing measurements will be handled using multiple imputation (MI). Arithmetic means will be used to describe cost data, and presented. In case of skewed cost data, non-parametric bootstrapping will be used to test for statistical differences in costs between the intervention and control group. The bootstrap replications will be used to calculate 95% confidence intervals around the costs (95% CI), based on the 2.5 and 97.5 percentiles. If cost data are distributed normally, t-tests will be used.

Concerning the cost measurements, a month of missing data exists between T2 and T3 and 6 months of missing data exists between T4 and T5. To deal with the issue we will use interpolation to construct new data points for these periods. This will be done by calculating mean cost data for the period of 6 months (T3) to 12 months (T4) post stroke and the period of 18 months to 24 (T5) months post stroke. These data will be used to estimate the period between 12 months to 18 months post stroke.

We will do a comparative analysis to estimate differences in costs between 1 year post stroke and 2 years post stroke. Additionally, we will compare cost outcomes and effect outcomes on the primary outcome scales. Furthermore, we will try to determine *high-cost users *and *low-cost users *of health care after stroke. In the latter analysis, *high-cost users *and *low-cost users *will be identified by specific patients' characteristics, costs being the dependent variable and patient characteristics being independent variables.

#### Record linkage study (RLS)

A RLS will be conducted in which the stroke cases registered in the Maastricht University Medical Centre (MUMC) Stroke Register, MUMC Medical Administration, the Mental Health Case Register (MHCR) and GP registrations in the same catchment area, will be linked. Since the available data linking these registers is limited, linking these databases will provide updated and extended information about the current estimates of care consumption and the hypothesis that problems occurring after stroke, such as depression, anxiety and dementia are underestimated and under-diagnosed. The aim of this study is to examine how patterns of health care consumption after stroke (in terms of health care costs, productivity costs, costs of informal care) change during the 5 years after stroke, in comparison with the 5 years before stroke and what the economic impact is of these changes from a societal perspective.

### Sample size calculation

Sample size calculation was not performed because all available patients will be used for data analysis.

### Setting and participants

As mentioned before, four stroke registers will be linked. The MUMC has been chosen because it is evident that the majority of stroke survivors in the area will be admitted to the hospital. Since the MUMC is the only (academic) hospital in that area, it is most likely that stroke patients will be registered in the MUMC database. The MUMC uses a general Medical Administration Database and a specific Stroke Database to collect data on stroke patients. In theory, these databases should overlap 100%, but further research should prove whether this is true. Therefore, we will use both databases capture all stroke cases registered. The organisations involved informed patients about data collection, which means that separate informed consent is not necessary for our record linkage. Approval for the use of these databases for this specific purpose will be requested from the Medical Ethics Committee of the University Hospital Maastricht and Maastricht University.

The MHCR has collected data cumulatively on the psychiatric hospital, the community mental health centre, the psychiatric department of the MUMC, the community psychiatric outreach team, psycho-geriatric nursing homes, sheltered housing, child psychiatric services, services for the mentally impaired, alcohol and drug abuse services etc. The MHCR has also collected demographic and diagnostic data in a region with a population of around 200,000. The region where this research will take place is a city of Maastricht (120,000 inhabitants), a relatively small city in the far south of the Netherlands, and its surrounding area (80,000 inhabitants).

The MUMC is the only hospital in the city of Maastricht and the surrounding area with both a regional and a top-referral care function. In the MUMC, all patients are registered with an ICD-9 or ICD-10 classification, depending on the year of admission.

### Timeline

In this RLS, changes in health care consumption during the five years after stroke in comparison with the five years before stroke and what the economic impact of these changes is, will be studied form a societal perspective. Stroke patients discharged from the MUMC between 2000 and 2005 will be included in this study, which will allow us to analyse patient data from 1995 until 2010 (analyses from5 years before first stroke case until 5 years after last stroke case).

### Cost analysis and valuation

Through anonymous record linkage health care consumption within the 10-year reference period (from 5 years before and after stroke) will be analysed. The first step in the analysis is to examine this consumption before, during and after stroke. In an additional analysis the health care costs will be calculated based on quantities derived from the MHCR and GP registrations. The updated Dutch manual for cost analysis in health care research [39] will be used for the valuation of these health care costs.

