## Methods

### Aim and research questions

The overall €-Restore4Stroke aim is to fully capture the economic impact of psychosocial care after stroke. Looking at the 4 subprojects embedded in this study, the following research questions will be answered:

• From a societal perspective, what are the costs and effects of the Self-Management intervention in comparison with an education intervention?

• From a societal perspective, what are the costs and effects of the Augmented CBT intervention in comparison with a computerized cognitive training intervention?

• How do patterns of care received after stroke (in terms of health care costs, productivity costs, costs of informal care) change during the time of the follow-up period of the Cohort study and what is their impact on the patient (in terms of health-related quality of life, life satisfaction and emotional functioning) in economic terms as well?

• How do patterns of health care consumption after stroke (in terms of health care costs, productivity costs, costs of informal care) change during the 5 years after stroke, in comparison with the 5 years before stroke and what is the economic impact of these changes from a societal perspective (record linkage study)?

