### €-Restore4Stroke outcome measures

All studies included in the €-Restore4Stroke project will be performed from a societal perspective meaning that all costs and outcomes of both the interventions and comparators will be included. Within the Restore4Stroke programme, Quality of life (QOL) is considered both from a general Health-Related Quality Of Life (HRQOL) and domain-specific QOL perspective. The general HRQOL perspective is operationalised as disease-specific HRQOL measured with the Stroke Specific Quality of Life (SS-QoL [15]), and generic HRQOL measured with the 5-dimensional EuroQol (EQ-5D [16]). The domain-specific perspective consists of the domains: participation measured with the Utrecht Scale for Evaluation and Revalidation Participation (*Utrechtse Schaal voor Evaluatie en revalidatie - Participatie *or USER-p [17]), emotional functioning measured with the Hospital Anxiety and Depression Scale (HADS [18]) and subjective well-being measured with 3 satisfaction questions. An overview of the primary and secondary outcome measures of all studies embedded in the Restore4Stroke programme is presented in Table 1.

**Table 1 T1:** Outcome measures Restore4Stroke (x: cost questionnaires, p: primary outcome measure, s: secondary outcome measure)

	Self-Management study				Augmented CBT study				Cohort study				
	T0	T1	T2	T3	T0	T1	T2	T3	T1	T2	T3	T4	T5

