### Statistical analysis

The statistical processing program SPSS will be used to link all databases. Databases will be linked anonymously, meaning that specific codes based on different variables will be computed and used to compare patients, instead of specific patient information. To estimate health care consumption before and after stroke, we will divide all stroke patients in 2 equal groups. Therefore, high-cost users of health care after stroke will be compared to low-cost users of health care after stroke. Similar as in the COI-study, we will estimate the differences between high-cost users and low-cost users using regression analysis.

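### The record linkage study asks for a societal before/after cost change, but it costs only part of health care, and its stated analysis compares high- with low-cost users after stroke

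*Protocol article*

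**What the plan says.** All references are to the Protocol article.

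- **Question.** The fourth item under Aim and research questions reads, in part: "patterns of health care consumption after stroke (in terms of health care costs, productivity costs, costs of informal care) change during the 5 years". The period meant is the one following the stroke, set against the 5 years preceding it. The opening of Record linkage study (RLS) repeats the three cost components and adds "what the economic impact is of these changes from a societal perspective". The RLS Timeline section repeats the societal perspective.
- **Perspective.** €-Restore4Stroke outcome measures says of all the sub-studies that they "will be performed from a societal perspective meaning that all costs and outcomes of both the interventions and comparators will be included".
- **Sources.** Four are linked: the MUMC Stroke Register, and then "MUMC Medical Administration, the Mental Health Case Register (MHCR) and GP registrations in the same catchment area, will be linked". For the two MUMC databases, the RLS Setting and participants section gives one purpose: "we will use both databases capture all stroke cases registered".
- **Costing.** RLS Cost analysis and valuation makes a description of consumption over the periods around the stroke the first step. It then adds a further analysis in which "the health care costs will be calculated based on quantities derived from the MHCR and GP registrations". Only health care costs are valued.
- **Analysis.** RLS Statistical analysis begins: "To estimate health care consumption before and after stroke, we will divide all stroke patients in 2 equal groups". It goes on to compare high- with low-cost users, both defined after stroke, by regression in the manner of the cost-of-illness study.

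**The concern.** There are two mismatches between the question and the method.

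The first is in the costs. The question and perspective promise three components, but the costing section delivers one, and that one in part. If the result is reported under the stated aim, a partial health-care cost would appear as the societal economic impact of stroke.

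The second is in the contrast. The question is about change over time within the stroke population. The sentence that introduces the method says it serves that purpose, but what follows is a comparison between patients in a single period. A team following the text would finish the specified analysis without having estimated the change it set out to measure.

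**Working it through.** No sample size or other figure is stated for this sub-study, so there is nothing to reproduce. The check sets the sections side by side.

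**Step 1: cost components asked for against sources named**

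| Component in the question | Source described | Costed? |
|---|---|---|
| Health care | Stroke Register, MUMC Medical Administration, Mental Health Case Register (MHCR), GP registrations | In part: MHCR and GP only |
| Productivity | None | No |
| Informal care | None | No |

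One of three components has a source. For that component, 2 of the 4 linked sources supply costed quantities.

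**Step 2: what the two costed sources cover.** RLS Setting and participants lists the MHCR's contents. They include the psychiatric hospital, the MUMC psychiatric department and psycho-geriatric nursing homes, so some hospital care is costed. General and acute MUMC care is not in that list, and GP registrations are not described as covering it. Patients enter the study by being discharged from the MUMC (RLS Timeline). Every included patient therefore has a MUMC stay that the stated costing leaves out.

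**Step 3: the contrast asked for against the contrast specified.** For patient *i*, let B_i be cost in the 5 years before stroke and A_i cost in the 5 years after.

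- Asked for: mean(A_i − B_i).
- Specified: mean(A_i among the higher-cost half) − mean(A_i among the lower-cost half), with a regression to explain the difference.

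B_i does not appear in the second expression. Suppose stroke changed nothing, so that A_i = B_i for every patient. The first quantity is then 0. The second is still positive whenever after-stroke costs vary, because the groups are formed on A_i. The specified comparison therefore carries no information on the before/after change.

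**Step 4: is the before/after change handled elsewhere?** RLS Cost analysis and valuation does announce an examination of consumption in the periods before, during and after the stroke. It attaches no comparison, estimate or interval to that step.

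**The case against.** The strongest reply is that this is a condensed article, and that the before/after examination is announced as the first step. The linked records span 1995 to 2010, so the data for it exist. Details of an announced comparison are commonly left to a fuller document. The first step is also not confined to MHCR and GP data; that restriction applies only to the additional costing. Finally, this is a register sub-study using all available patients, and nothing in it touches either randomised trial.

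Much of this stands. It rules out saying that the study cannot answer its question at all: change in health care use could be described from the linked data. It does not remove the mismatch. The article is not merely silent on method; it names one for the before/after purpose, and that method estimates something else. The gap between the societal question and the health-care costing is a contradiction in the text, not an omitted detail.

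Three stronger readings are tempting and are not supported:

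- **No hospital costs at all.** The MHCR covers psychiatric hospital care. What is missing is general and acute MUMC care.
- **The cost scale is thrown away by the two-group split.** The regression is tied to the cost-of-illness study, whose Statistical analysis section makes costs the dependent variable. The wording is ambiguous at most.
- **Deaths after stroke bias the before/after comparison by a known amount.** The article does not say that unadjusted 5-year totals will be compared. The share dying given in the Background covers stroke in general and has no time horizon, whereas this study includes patients discharged from hospital. Zero cost after death is also a real part of total cost to society. Whether to analyse totals or cost per time alive is a choice of estimand on which statisticians can differ.

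**Conclusion.** The point holds in limited form and should be fixed. Two of the three cost components in the question have no described source. The third omits general and acute MUMC care, including the stroke admission, although the MUMC Medical Administration is linked. The only comparison specified for the before/after purpose is between high- and low-cost users after stroke, which cannot give a before/after change.

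This assumes that the registers hold no more than the article describes, and that the costing sentence lists its sources completely. The size in euros cannot be derived from the article. Leaving out the stroke admission lowers the cost recorded at or after stroke. Other MUMC care is missing on both sides of the comparison, so the net effect on the estimated change is not known.

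**What to change.** 1. Restate the question and perspective of this sub-study as health-care costs, in Aim and research questions and in the RLS sections. Alternatively, name data sources for productivity and informal-care costs. Exempt this sub-study from the general statement on societal perspective if the first option is taken.
2. Add quantities from the MUMC Medical Administration to the costing, and state to which period the stroke admission is assigned.
3. For the before/after question, specify the within-patient after-minus-before difference in cost. Give a percentile confidence interval from a paired bootstrap that resamples patients and keeps both of their periods together. Percentile bootstrap intervals are already used for costs elsewhere in the article. Report time alive after stroke alongside, so that readers can see how much follow-up the after-period contains.
4. Present the high/low-cost user analysis as a separate secondary analysis with its own stated purpose, and say explicitly that cost is the dependent variable if that is intended.

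The cost is rewording, some extra costing work on data already being linked, and a narrower claim if the health-care perspective is chosen. Naming new sources for the other two components would cost more. The timing is favourable: approval to use the databases is still to be requested, and the project has not quite finished its preparation phase.

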### Statistical analysis

The statistical processing program SPSS will be used to link all databases. Databases will be linked anonymously, meaning that specific codes based on different variables will be computed and used to compare patients, instead of specific patient information. To estimate health care consumption before and after stroke, we will divide all stroke patients in 2 equal groups. Therefore, high-cost users of health care after stroke will be compared to low-cost users of health care after stroke. Similar as in the COI-study, we will estimate the differences between high-cost users and low-cost users using regression analysis.

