## Background

Stroke has a major socio-economic impact worldwide and is the leading cause of disabilities in the Western world. It is estimated that the worldwide prevalence of stroke is 0.2% of the world population. Of the people who suffer from a stroke, 30% die, 30% are left functionally disabled and 40% have a successful recovery with minor to no disabilities [1]. It is estimated that by 2023 the absolute number of patients experiencing a first stroke will increase, in comparison with 1983, by 30% worldwide [2]. The disease impact of stroke is considerable on stroke patients and on their informal caregivers. More than 50% of the stroke survivors return to their homes after being discharged from the hospital [3]. At home, these survivors and their informal caregivers have to deal with the long term consequences of stroke, which are seen in physical, psychological and social areas of functioning [4,5].

Not only the clinical, but also the financial burden of stroke is considerable [6]. Currently, approximately 3-4% of total health care expenditures in Western countries are spent on stroke [7]. On the one hand, governments are cutting down on expenditures for health care, while on the other hand the health care sector is facing an increased demand for stroke care, due to demographic changes (e.g. an aging population) and changing attitudes towards health care (e.g. more demanding society; value for money) [8]. The growing demand for stroke care and the limited resources available for health care, have led to an increased interest in the economic aspects of stroke. The last few years have shown a remarkable increase in the publication of economic studies on stroke [7]. A Pubmed search combining "Cerebrovascular disorders" and "Costs and cost-analysis" shows that since 1990 the number of stroke studies including costs have increased in both absolute and relative terms. Figure 1 shows this development from 1990 until 2010, the last year for which complete data were available.

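### Record linkage study: fixed five-year windows and an equal high-cost/low-cost split of all patients have no observed-time basis, so death or departure can distort both results

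*Protocol article*

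**What the plan says.** All references are to the record linkage study (RLS) part of the Protocol article unless stated otherwise.

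- **Who is included.** Timeline: "Stroke patients discharged from the MUMC between 2000 and 2005 will be included in this study". Sample size calculation: "Sample size calculation was not performed because all available patients will be used for data analysis". Neither sets a condition on survival or residence.
- **Which window.** Cost analysis and valuation: "health care consumption within the 10-year reference period (from 5 years before and after stroke) will be analysed". Timeline adds the calendar range: "which will allow us to analyse patient data from 1995 until 2010".
- **How patients are grouped.** Statistical analysis: "To estimate health care consumption before and after stroke, we will divide all stroke patients in 2 equal groups", and then "high-cost users of health care after stroke will be compared to low-cost users of health care after stroke", with regression to describe the difference.
- **What is costed.** Cost analysis and valuation, for the additional cost analysis: "the health care costs will be calculated based on quantities derived from the MHCR and GP registrations".
- **What is linked.** The opening RLS paragraph names two databases of one hospital, a regional mental health register and GP registrations in the same area. No death or population register is named.

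These sections do not mention death, moving away, register entry, censoring or person-time.

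**The concern.** Taken together, these sections state a rule: all discharged patients, a fixed window on each side of the stroke, and two equal halves by cost after stroke. The two windows are not alike. A patient who has a stroke has, by definition, survived the preceding five years; survival of the following five is not guaranteed. The Background itself notes "Of the people who suffer from a stroke, 30% die, 30% are left functionally disabled".

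A patient who dies or leaves the area stops generating records, and in a register that looks the same as not using care. The missing-data rules for the trials and the cost-of-illness study are not carried over to this study. They would not catch the problem anyway, because an absent register event is not a missing value.

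Both results of the sub-study are exposed. The before-after change may mix change in use with loss of observed time. The low-cost half may mix people who need little care with people who were observed only briefly, so a regression on that grouping would partly describe survival and departure. The cost split is further exposed because it draws only on mental health and GP quantities, so an early death may carry little recorded cost.

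**Working it through.** **The plan's own figure.** Discharges in 2000-2005 with five years on each side give 2000 - 5 = 1995 and 2005 + 5 = 2010. This reproduces the stated calendar range. Administrative follow-up is therefore long enough, and the gap concerns only death, departure and late entry.

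**Inputs.** The article gives neither the share who die or leave within five years of discharge nor their yearly cost. Assumed here: exit share S of 10%, 30% or 50%; a constant exit rate; others' yearly cost set to 1 before and after stroke. No late entry is modelled.

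**Observed time.** The exit rate is λ = -ln(1 - S)/5. The mean observed time of those who exit is m = 1/λ - 5(1 - S)/S. For S = 0.30: λ = 0.0713 and m = 14.02 - 11.67 = 2.35 years. Observed share of the window = [(1 - S) × 5 + S × m]/5 = (3.5 + 0.706)/5 = 0.841.

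**Apparent change in the five-year total.** If those who exit cost the same per year as others, before and after, the true change is zero and the apparent change equals the observed share minus 1. If they cost r times as much per year after stroke only, the ratio is [(1 - S) × 5 + S × r × m]/5. The total shows no change when r = 5/m.

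| Exit S | m (years) | Observed share | Apparent change, r = 1 | Apparent change, r = 2 | r giving no change |
|---|---|---|---|---|---|
| 10% | 2.46 | 94.9% | -5% | -0.2% | 2.04 |
| 30% | 2.35 | 84.1% | -16% | -2% | 2.13 |
| 50% | 2.21 | 72.1% | -28% | -6% | 2.26 |

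**Effect on the two halves.** In a simulation of 400,000 patients (lognormal yearly cost, coefficient of variation 0.5 to 1.5, split at the median of the five-year total):

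- With r = 1, 67-84% of those who exit fall in the low half across the three exit shares. Split by cost per observed year, about 50% do.
- With r = 1 and 30% exit, they make up 42-49% of the low half and 11-18% of the high half. Compared with a per-year split, 13-19% of all patients change half.
- With r = 2 and 30% exit, about 56% of those who exit fall in the low half, although only 14-33% would by yearly cost.

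**What the small change at r = 2 means.** At 30% exit the total is (3.5 + 0.3 × 2 × 2.35)/5 = 0.982, hence -2%. Per observed person-year the figure is 0.982/0.841 = 1.17, so a 17% rise is hidden. If those who exit cost twice as much both before and after stroke, the before value is 0.7 + 0.3 × 2 = 1.3 and the ratio is 0.982/1.3 = 0.76: an apparent fall of 24% with no true change in anyone's yearly use.

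**The case against.** The strongest reply is that the article is silent rather than wrong. It does not say that every patient is taken to have five post-stroke years, or that an early death is handled as five years of almost no use. Nor does it say whether the split uses a total or a yearly cost. A fuller plan could settle this. That is right as far as it goes, and a reader who infers a stated five-year assumption goes beyond the text. What remains is that the rule as published covers all patients, equal halves and a fixed window. Adding person-time, a survivor restriction or a separate group for deaths would alter that rule.

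Four further objections stand in part:

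- **Mortality.** The Background's 30% has no time horizon and covers all strokes, not patients discharged alive. It cannot serve as five-year mortality here.
- **Choice of estimand.** For cumulative societal cost per patient, zero cost after death is correct. It misleads only when read as a change in consumption pattern or as a type of user. For patients who leave, recorded zeros are missing data under either reading.
- **Pre-stroke window.** Survival is assured but register coverage is not. People who moved in or joined a linked practice late have shortened pre-stroke records, which pulls the comparison the other way.
- **Cost sources.** The restriction to mental health and GP quantities belongs to the additional cost analysis. It affects the cost split, not the first-step comparison of consumption.

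**Conclusion.** The point holds as a flaw in a stated analysis rule: the before-after comparison and the high/low split rest on fixed windows with no observed-time basis. The apparent changes of -5%, -16% and -28%, and the 67-84% of those who exit who land in the low half, are illustrations. They assume 10%, 30% and 50% exit, a constant exit rate, equal yearly cost, no true change, no late register entry and analysis of five-year totals.

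A reader might infer that the change is certainly biased downward, or that predictors of death will necessarily appear as predictors of low use. The documents support neither. Late register entry works in the opposite direction, and the total can be nearly unchanged when those who exit cost about twice as much per year after stroke. Misclassification between the halves remains in that last case (56% in the low half against 14-33% by yearly cost), so the grouping problem is firmer than the direction of the before-after bias.

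**What to change.** In the RLS sections Cost analysis and valuation and Statistical analysis:

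1. Define an observation period for each patient: from register entry (or five years before stroke, if later) to death, departure from the registers or five years after stroke, whichever comes first. State how each date is obtained, using the hospital and GP sources where they hold it.
2. Report consumption and cost per observed person-year before and after stroke.
3. Base the high/low split and the regression on cost per observed year, or on patients observed for the full five years. Report those who died or left as a separate group.
4. If a cumulative five-year cost is wanted, report it separately, with death as true zero cost and departure as censoring, using a censoring-adjusted cost estimator.

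The cost is extraction of entry and exit dates, some extra analysis, and smaller or additional groups. A restriction to fully observed patients also limits that comparison to survivors who stayed. The documents do not show that the dates are available, and linkage is to be anonymous, so they should be specified before the extract is made; they may be hard to recover later.
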